#### Secondary study outcomes

For patients treated with prostatectomy, time from a BCR to prostate cancer retreatment decision-making will be evaluated by Kaplan-Meier methods including log-rank tests as well as multivariable Cox proportional hazards regression. Non-proportionality of hazards will be assessed by Schoenfeld residuals. In exploratory analyses, we will perform subgroup analyses by patient characteristics (e.g.: clinical stage: ≤ cT2b-c or cT3).

Scores for the APECC, EORTC QLQ-C30 and QLQ-PR25, MAX-PC, NCQ, EQ-5D-5L questionnaires will be calculated according to published scoring algorithms. Between-group differences over time in mean scores will be tested using a mixed effects modelling approach. For the moderation analysis, a regression based model will be constructed for each potential moderator separately in order to estimate the conditional (interaction) effect. Standardized effect sizes will be calculated by dividing the difference in mean change scores from baseline to follow-up between groups by the pooled baseline standard deviation.

The cost-effectiveness analysis will compare the costs and health benefits between both groups. This comparison is typically expressed in incremental cost, − health effects (often quality-adjusted life-years or QALYs), and - cost-effectiveness ratio (ICER) (e.g., incremental cost per QALY gained). A societal perspective from the Netherlands, plus lifelong time horizon will be adopted, according to the Dutch guidelines [54]. A trial-based analysis will be combined with a Markov decision analytic model, in order to capture both the trial endpoints at 2 years follow-up as well as the life long time horizon. Using a monthly cycle length, the model will simulate the lifelong course of events in a hypothetical cohort of prostate cancer survivors. We will include the estimation of the degree of uncertainty about each input parameter and the use of (probabilistic) sensitivity analyses. We will apply the most relevant severity-based ceiling ratio between €20,000 and €80,000 per QALY [55]. If necessary, Value of Information (VOI) analysis will be performed to support decision-making regarding adoption and further research [56].

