Currently in most Western countries, patients who have completed primary treatment for localized prostate cancer are often included in a specialist-based follow-up care program at the hospital. Routine follow-up care for localized prostate cancer survivors includes periodic visits to test the prostate specific antigen (PSA) [8–10]. A detectable PSA level after prostatectomy is considered a biochemical recurrence (BCR). In clinical care, BCR can (in 16–35% of cases) trigger secondary therapy for prostate cancer, including salvage local treatment or androgen deprivation therapy (ADT) [11, 12]. Managing long-term and late treatment effects and providing psychosocial support to maintain health-related quality of life (HRQOL) are also important goals of survivorship care. After primary treatment, many prostate cancer survivors experience late effects of treatment, including urinary symptoms, bowel symptoms, sexual dysfunction, symptoms related to androgen ablation, and adverse psychosocial and relationship effects [13–19].

In order to address the needs of the growing population of prostate cancer survivors in the long-term, current survivorship care models are unsustainable [1]. Different models of follow-up care for cancer patients have been proposed. There is evidence that follow-up care for cancer patients can be provided by medical specialists, general practitioners (GPs), nurses, or by sharing the care among a multidisciplinary team [20–30]. Intervention studies for chronic diseases, such as diabetes or cardiovascular disease, suggest that it is possible to coordinate follow-up between primary- and secondary care providers [31–33]. GPs, who traditionally play a crucial role in providing continuous and comprehensive care for most patients with chronic diseases, could similarly consider the role of providing follow-up care to cancer survivors. National health councils of the United States, the United Kingdom, and the Netherlands have advised giving primary health care professionals a greater role in the follow-up of cancer survivors [1, 3, 34, 35]. This is supported by evidence from randomized controlled trials of patients with breast and colorectal cancer that have shown no significant differences in adverse outcomes for patients between primary versus secondary follow-up care [23, 25–27].

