#### Secondary study outcomes

The time from a BCR to prostate cancer retreatment decision-making will be assessed at T0, T1 and T3. This is defined as the time from a rising PSA level after surgery (> 0.2 ng/mL) with or without radiotherapy or a rising PSA level of 2 ng/mL over the post-treatment nadir after radiotherapy to the decision regarding prostate cancer retreatment.

Other secondary outcome measures will assess the self-reported management of treatment-related side effects, health-related quality of life, prostate cancer-related quality of life, prostate cancer-related anxiety, and cost-effectiveness as described in Table 2. They will be assessed at T0, T1, T2, and T3 time points. Perceived continuity of care will be assessed in the T2 questionnaire.

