#### Adherence to the prostate cancer surveillance guideline and time from a BCR to prostate cancer retreatment decision making

With a sample of 270 patients who have been treated with prostatectomy, the prospective design will allow for testing of the main effect of GP-based versus specialist-based follow-up care on adherence to the prostate surveillance guideline, as represented by the timing and frequency of PSA assessments. It is expected that 90% of the patients in the usual care group will be assessed according to the guideline, defined as 4 PSA measurements in the study period of 2 years. This is in line with the observed adherence to PSA testing recommendations in a previous randomized controlled trial of shared care for follow-up of men with prostate cancer [24]. We consider an adherence percentage as low as 80% (10 percentage points non-inferiority margin) in the GP-based group as acceptable and lower adherence percentages as unacceptable. With 270 prostatectomy patients we have 86% power at a one-sided significance level of 5%.

We will also evaluate the difference between arms in time from a BCR to prostate cancer retreatment decision-making. Based on data of a retrospective cohort study of 1340 patients who were treated with prostatectomy at the Antoni van Leeuwenhoek Hospital and expert opinion, an acceptable mean time to decision-making is thought to be 30 days. We will evaluate whether the time to decision-making is substantially longer in the GP-arm than the specialist-based arm. We consider the maximally acceptable average time to decision-making in the GP-based arm as 90 days (60 days non-inferiority margin). In the absence of empirical data on the standard deviation (SD) for the time to decision-making, we assume an SD of 20 days in the specialist-arm and 60 days in the GP-arm. With 270 prostatectomy patients we expect a total of 7 patients with a BCR in each arm, which enables us to investigate the time from a BCR to prostate cancer retreatment decision making.

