### Safety reporting

An independent safety committee is formed to review safety-related data of patients participating in the PROSPEC study. The safety committee consists of an epidemiologist, a urologist and a GP. All of the committee members are independent of the study, and none has a conflict of interest with the sponsor of the study. During inclusion, the safety committee will meet twice: when 20 and 100 patients have finished the first 12 months of the intervention. The safety committee will advise the study investigators on the compliance to the prostate surveillance guideline, represented by the number of PSA measurements (primary endpoint), the time from a BCR to prostate cancer retreatment decision-making (main secondary endpoint), and the number of adverse events caused by following the study protocol.

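### The main secondary endpoint has a 60-day non-inferiority margin on a mean, but the planned log-rank and Cox analyses compare hazards and give no comparison with 60 days

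*Protocol article*

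**What the plan says.** All references are to the protocol article.

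- **Rank.** Safety reporting names the endpoint as "the time from a BCR to prostate cancer retreatment decision-making (main secondary endpoint") and has the safety committee advise on it.
- **Criterion.** Under Power calculation, "an acceptable mean time to decision-making is thought to be 30 days". Then: "We consider the maximally acceptable average time to decision-making in the GP-based arm as 90 days (60 days non-inferiority margin"). For the spread, "we assume an SD of 20 days in the specialist-arm and 60 days in the GP-arm".
- **Size.** Among the 270 prostatectomy patients, "we expect a total of 7 patients with a BCR in each arm". No significance level or power is given for this endpoint; the one-sided 5% and 86% in the same subsection belong to PSA adherence.
- **Analysis.** Under Data analysis, the endpoint in prostatectomy patients "will be evaluated by Kaplan-Meier methods including log-rank tests as well as multivariable Cox proportional hazards regression", with Schoenfeld residuals to check proportionality and exploratory subgroup analyses. No hazard-ratio margin, mean difference or confidence limit is mentioned.
- **Event.** The Secondary study outcomes text under Study outcomes runs the clock "to the decision regarding prostate cancer retreatment". Table 2 instead has the decision of retreatment, which can be read more narrowly. Both start the clock at a PSA value above a threshold.

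**The concern.** The criterion is a difference in means in days. The analysis is a comparison of hazards. The document states both, and they do not fit together, so this is more than a detail left for a later plan.

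A log-rank p-value above 0.05 does not establish non-inferiority, and one below 0.05 does not show that the margin was exceeded. The Discussion adds to the risk by hypothesising that the arms will not differ significantly on this endpoint, which invites a null log-rank test to be read as support for GP-based care. At stake is the trial's conclusion on whether GP follow-up delays the retreatment decision.

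**Working it through.** **Inputs (Power calculation).** Means 30 and at most 90 days; margin 60 days; SDs 20 and 60 days; 7 BCRs per arm, an implied rate of 7/135 = 5.2%. One-sided 5% is borrowed from the adherence endpoint as an assumption.

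**1. The plan's own figure.** The expected 7 per arm cannot be derived, since no BCR rate is given. It does match the size for a mean-based non-inferiority test with 80% power (assumed) and equal true means:

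n per arm = (20² + 60²)(1.645 + 0.842)² / 60² = 4000 × 6.18 / 3600 = 6.9, rounded up to 7.

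The planning figures therefore fit a comparison of means.

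**2. What a mean-based test would deliver with 7 per arm.**
- SE = √(400/7 + 3600/7) = √571.4 = 23.9 days.
- Welch df = (57.1 + 514.3)² / (57.1²/6 + 514.3²/6) = 7.3.
- One-sided 95% half-width = 1.88 × 23.9 = 45 days. Two-sided 95% half-width = 2.34 × 23.9 = 56 days.
- Power if the true means are equal: 81% by normal approximation (60/23.9 − 1.645 = 0.87), 73% by noncentral t with Welch df. At one-sided 2.5% the Welch figure is 59%.
- Power if the true difference is 30 days: 31% (Welch) to 35% (normal).

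**3. What the planned log-rank test does.** Simulation with 7 per arm, every BCR reaching a decision, two-sided 5%, specialist times with mean 30 and SD 20, GP times with SD 60. The gamma case was rerun with 100,000 replicates.

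| GP mean | Position against the margin | Log-rank rejects, gamma | Log-rank rejects, lognormal |
|---|---|---|---|
| 30 days | no difference in means | about 17% | about 15% |
| 60 days | inside the margin | about 24% | about 31% |
| 90 days | at the margin | about 80% | about 85% |

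At equal means the rejections are almost all in favour of the GP arm: a gamma distribution with mean 30 and SD 60 puts most times very early and a few very late, which the log-rank test reads as faster decisions. At 60 days the test often signals a difference that the plan accepts. At 90 days it misses about 20% (gamma) or 15% (lognormal).

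**4. Cox.** With 14 events split evenly and a hazard ratio of 1, the 95% interval is exp(±1.96 × 2/√14) = 0.35 to 2.85, before any covariate is added. Fourteen events support hardly more than one covariate.

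**5. A caution on the replacement.** In the same simulations at a GP mean of 90 days, a plain Welch upper limit falls below 60 days in about 10% of gamma trials (about 12% lognormal), against the nominal 5%. Skewed times in samples of 7 make the ordinary limit too lenient.

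**The case against.** The best defence is that this is a secondary endpoint in a condensed article, that no power is claimed for it, and that a restricted mean with a confidence limit can be read from Kaplan-Meier curves, a detail often left to an analysis plan that is not shown. Part of this stands: Kaplan-Meier estimation is compatible with the margin. The article nevertheless names the tests, and those tests do not address the margin it sets.

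Several stronger readings are tempting, and the document does not support them:

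- **That 14 patients make the margin untestable.** They do not; step 2 gives 73% to 81% power on the plan's own SDs. Fourteen is also an expectation and not a ceiling.
- **That log-rank misses an unacceptable GP arm about half the time.** A miss rate of 54% at means of 30 and 90 days needs exponential times, whose SDs would be 30 and 90 and so contradict the stated 20 and 60. A 90-day mean is also described as the most that is acceptable, so it is the edge of acceptance.
- **That only 2 to 5 events will occur.** This applies the Background remark that "BCR can (in 16–35% of cases) trigger secondary therapy for prostate cancer" to 14 BCRs (2.2 to 4.9). That remark is not a planning input, and the endpoint is named throughout for decision-making. It holds only on the narrow reading of Table 2.
- **That late or missed PSA tests go unseen in the trial.** They do not enter this endpoint, but the timing and frequency of PSA tests are the primary outcome. Starting at BCR is the question the article poses.
- **That radiotherapy patients are wrongly dropped.** The Power calculation plans this endpoint in the prostatectomy patients.

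**Conclusion.** The concern holds in this limited form: the stated margin is on a mean in days, the named tests address hazards, and no result of those tests shows whether the margin is met. The size is the pattern in step 3: roughly 15% to 17% rejection at equal means, 24% to 31% inside the margin, and 15% to 20% missed at the margin. The multivariable Cox model is not supportable on about 14 expected events.

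The figures rest on the plan's means, SDs and 7 BCRs per arm, on gamma or lognormal times, on a GP SD that stays at 60 days whatever the mean, and on no censoring. The exact percentages move with these choices; the mismatch of scale does not. The comparison is conditional on a detected BCR, which limits what the result means without preventing a test of the margin.

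**What to change.** In Data analysis, Secondary study outcomes:

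1. Make the main analysis the GP-minus-specialist difference in mean time to decision, or in restricted mean with a pre-specified horizon, among prostatectomy patients with BCR. Compare its one-sided 95% upper limit with 60 days. The choice of level for this endpoint should be stated.
2. Use an interval that allows for unequal variances and skewed times, and check its error rate at the margin by simulation, because the plain Welch limit gives about 10% there.
3. Report log-rank, Cox and subgroup results as descriptive only.
4. Align Table 2 with the text under Study outcomes, so that the event is the dated decision regarding retreatment, including a decision not to retreat.
5. State the expected precision: one-sided half-width about 45 days, two-sided about 56 days, about 73% power by Welch if the true means are equal.
6. State that the comparison is conditional on a detected BCR, and that delay from late or missed PSA tests is reflected only in the primary adherence outcome.

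A companion analysis of time from randomisation to first retreatment decision is not a good substitute, since it mixes recurrence incidence with delay.

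The cost is a change of wording and one analysis of dates that are already being abstracted. The downside is that the reported precision will look poor.

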### Ethical approval and consent to participate

The study received ethical approval from the institutional review board of the Antoni van Leeuwenhoek hospital, a specialized cancer center located in Amsterdam, the Netherlands (METC18.0033/M17PRO). The trial is registered in the Netherlands Trial Registry (NTR 7266). All patients will provide written informed consent before participating in the study.

### Safety reporting

An independent safety committee is formed to review safety-related data of patients participating in the PROSPEC study. The safety committee consists of an epidemiologist, a urologist and a GP. All of the committee members are independent of the study, and none has a conflict of interest with the sponsor of the study. During inclusion, the safety committee will meet twice: when 20 and 100 patients have finished the first 12 months of the intervention. The safety committee will advise the study investigators on the compliance to the prostate surveillance guideline, represented by the number of PSA measurements (primary endpoint), the time from a BCR to prostate cancer retreatment decision-making (main secondary endpoint), and the number of adverse events caused by following the study protocol.

## Discussion

In order to care for the needs of the increasing number of prostate cancer survivors, a more comprehensive and sustainable follow-up care model is necessary. GPs play an essential role in providing continuous and comprehensive care, and could consider the role of providing follow-up care to some cancer survivors. The evidence in the studies conducted, to date, have been limited, focusing on other cancer sites, or on shared follow-up care models. In the current study, we are evaluating a GP-based follow-up care model for men treated for localized prostate cancer (prostatectomy or radiotherapy).

It is hypothesized that GP-based follow-up care will not differ significantly with specialist-based follow-up care regarding the adherence to the prostate surveillance guideline regarding: the number of PSA measurements; the time from a BCR to prostate cancer retreatment decision-making; the management of treatment-related side effects as experienced by patients; health-related quality of life and prostate cancer-related anxiety; continuity of care and; and costs-effectiveness.

Several limitations of the trial should be noted. Prostate cancer patients will be followed up for a period of 2 years, meaning that longer-term evaluation of outcomes will not be possible. The time frame of the study is limited by the available research funding. We also recognize that not all medically eligible patients will be willing to be randomized to GP-based or specialist-based follow-up care, resulting in a study sample composed of men who have no strong preference in this regard. We will monitor the number of patients who decline to participate in the study, and the reasons for not participating, when possible.

This trial has several notable strengths, including its multicenter, randomized design, the use of an intention-to-treat strategy for the data analysis, and the inclusion of a cost-effectiveness analysis. The trial has a pragmatic character, as current practice is compared with GP-based care in the real-world healthcare system. Moreover, a process evaluation will be executed alongside this trial in order to understand and identify factors that influence GP-based follow-up care. If our trial indicates that a GP-based follow-up care is cost-effective, the process evaluation will help to describe the actual exposure to the intervention and to understand the barriers and facilitators to support effective implementation.

In conclusion, the PROSPEC trial will provide empirical evidence regarding the viability and effectiveness of a GP-based follow-up care program for localized prostate cancer patients. Especially within the current context of the rising number of prostate cancer survivors and the demands for a more comprehensive and sustainable follow-up care model, this type of research is of paramount importance as it can contribute to resolving some of the current challenges facing cancer survivorship care. If primary care-based follow-up for prostate cancer patients is feasible, the findings would also hopefully be of relevance to other groups of cancer survivors.

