### Objectives and hypotheses

This multicenter, randomized, non-inferiority trial, the PROSPEC study, is designed to compare the (cost-) effectiveness of a GP-based versus a specialist-based follow-up care program for localized prostate cancer survivors. We hypothesize that GP-based follow-up is as effective as specialist-based follow-up care in terms of (1) adherence to the prostate surveillance guideline regarding the timing and frequency of PSA measurements; (2) the time from a BCR to prostate cancer retreatment decision-making; (3) the management of treatment-related side effects, as experienced by patients; (4) health-related quality of life and prostate cancer-related anxiety; (5) continuity of care and; (6) costs-effectiveness.

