#### The management of treatment-related side effects as experienced by patients

With a sample of 120 patients who have been treated with radiotherapy, we are able to test the management of treatment-related side effects as experienced by patients. Hence, we will focus on questions from three scales of the “Assessment of Patients’ Experience of Cancer Care (APECC) survey” (information exchange; physicians’ affective behavior; and physicians’ knowledge) [44]. We will use the mean score of those three scales to measure patient satisfaction with the follow-up care. Arora and colleagues observed SDs between 15.8 and 24.9 for these three scales [44]. We assume that these SDs are generalizable to our hospital patient group. For a SD of 15.8, power is 80% to detect a clinically relevant difference of 8.1 points (effect size = 8.1/15.8 = .51) with 60 patients in each group (two-sided alpha 5%) [53].

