#### Patient-reported outcomes

For the patient-reported outcomes (e.g. HRQOL, prostate-specific anxiety, etc.) we will compare changes in mean questionnaire scores over time between the usual care and the intervention group. Based on 390 patients and a survey attrition of 20%, power is at least 80% to detect a difference in questionnaire-based outcomes between patients who had their follow-up at their GP or specialist with an effect size of 0.1, at a two sided-significance level of 5%. With this sample size we will be able to detect clinically meaningful differences [53].

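### Patient-reported outcomes are hypothesized to be equally good under GP care, but only two-sided difference tests without a margin are planned for them

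*Protocol article*

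**What the plan says.** Under Objectives and hypotheses the trial is described thus: "This multicenter, randomized, non-inferiority trial, the PROSPEC study, is designed to compare the (cost-) effectiveness". The hypotheses follow: "We hypothesize that GP-based follow-up is as effective as specialist-based follow-up care in terms of" six items. Item 3 is side-effect management as patients experience it, item 4 is health-related quality of life and anxiety, and item 5 is continuity of care. The Discussion restates the same list as "It is hypothesized that GP-based follow-up care will not differ significantly with specialist-based follow-up care".

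The Power calculation section sets non-inferiority margins for two outcomes: 10 percentage points for guideline adherence (one-sided 5%) and 60 days for time from biochemical recurrence to retreatment decision. For the patient-reported outcomes it is framed differently:

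- APECC mean score, 60 radiotherapy patients per arm, two-sided 5%: "For a SD of 15.8, power is 80% to detect a clinically relevant difference of 8.1 points".
- Other questionnaires, 390 patients with 20% attrition, two-sided 5%: "power is at least 80% to detect a difference in questionnaire-based outcomes".

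Data analysis, Secondary study outcomes, gives the method: "Between-group differences over time in mean scores will be tested using a mixed effects modelling approach". It adds standardized effect sizes for change from baseline. It states no margin or confidence-bound rule for these scores.

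**The concern.** A test for a difference answers whether the arms can be told apart. It does not answer whether a relevant deficit has been ruled out, which is what a claim of equal effectiveness needs. If the hypothesis is that no significant difference appears, then small numbers, missing questionnaires and noisy scores all make it easier to satisfy.

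The protocol does use margins elsewhere, and one of the two belongs to a secondary outcome (time to decision), so secondary status alone does not explain their absence here. It also names a clinically relevant APECC difference, but only as something to detect, not as something to exclude. At stake is what the trial may conclude about patients' experience of GP follow-up. The primary endpoint is not touched by this point.

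**Working it through.** **Inputs from the protocol.** APECC difference 8.1 points; SD 15.8 used in the calculation, where the source study "observed SDs between 15.8 and 24.9 for these three scales"; 60 per arm; two-sided 5%. Other questionnaires: 390 × 0.80 = 312 evaluable, or 156 per arm under 1:1 allocation.

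**Formulas.** Two-group comparison at one time point, as in the protocol's own calculation. SE = SD × √(2/n). Noncentrality δ = 8.1/SE. Power = P(T > t critical), where T is noncentral t with 2n − 2 degrees of freedom and noncentrality δ. The chance that a true 8.1-point deficit is non-significant is 1 − power.

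**Step 1: reproduce the stated 80%.** SE = 15.8 × √(2/60) = 2.885; δ = 8.1/2.885 = 2.808; critical t (118 df) = 1.980. Power is 79.5%, or 80.2% by the normal approximation. The stated figure reproduces, and it is power for a two-sided test of difference.

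**Step 2: largest SD the score can have.** The outcome is the mean of three scales. The SD of a mean of scales cannot exceed the mean of their SDs, and reaches it only under perfect correlation. If 15.8 and 24.9 are the smallest and largest of the three, the bound is (15.8 + 24.9 + 24.9)/3 = 65.6/3 = 21.9.

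**Step 3: chance that a true 8.1-point deficit is non-significant.**

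| n per arm | SD | SE | δ | Non-significant |
|---|---|---|---|---|
| 60 | 15.8 | 2.885 | 2.808 | 20% |
| 60 | 21.9 | 3.998 | 2.026 | 48% |
| 156 | 15.8 | 1.789 | 4.528 | 0.5% |
| 156 | 21.9 | 2.480 | 3.267 | 10% |

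The lower two rows apply if the APECC is analysed in all patients after 20% attrition. If instead the same attrition hit the radiotherapy patients alone (an assumption, since the APECC calculation makes no allowance for it), 60 × 0.80 = 48 per arm, and the 20% at SD 15.8 becomes 30%. Losing data makes the hypothesis easier to meet.

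**Step 4: what a margin rule would do.** Take 8.1 points as the margin, true equality and a one-sided 5% level. Power = P(T > t critical) with the same δ and critical t (118 df) = 1.658. With 60 per arm it is 87% at SD 15.8 and 64% at SD 21.9. A true deficit equal to the margin would be accepted 5% of the time, instead of 20% to 48%.

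**The case against.** The strongest reply is that no decision rule is printed. A reader might infer that the protocol treats p > 0.05 as proof of equivalence, but no sentence says so. That reading rests on one Discussion sentence, which covers adherence and time to decision in the same breath although both have margins, so it may be loose shorthand. The protocol also plans standardized effect sizes, and the mixed model will yield confidence intervals. Two-sided testing of secondary outcomes in a non-inferiority trial is not in itself an error, and success rules for such scales are often left to the statistical analysis plan. This stands as a limit on the point. It does not remove it, because the protocol itself fixes the hypothesis wording, the type of test and its sidedness, and these do not fit together.

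Three stronger numerical readings also fail:

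- Using SD 24.9 for the APECC score would give a larger miss rate, but that SD belongs to at most single scales and cannot apply to a mean that includes a scale with SD 15.8.
- Calling 0.1 SD the protocol's clinically meaningful difference, and computing a miss rate from it, is not supported. The effect size of 0.1 is given without a metric.
- No firm miss rate can be attached to quality of life or anxiety. With 156 per arm, a deficit of 0.3 SD is missed 25% of the time in an unadjusted comparison at one time point. With a baseline-adjusted mean of three follow-ups at an assumed correlation of 0.5, it is missed 2% of the time.

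The APECC figures at 60 per arm likewise assume that only radiotherapy patients are analysed. The power section sizes on them, but the outcome and analysis sections set no such restriction.

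**Conclusion.** The mismatch holds. Equal effectiveness is hypothesized for the patient-reported outcomes, and the planned tests can only look for a difference. Its size for the APECC score is a 20% to 48% chance that a deficit the protocol calls clinically relevant comes out non-significant with 60 per arm, or 0.5% to 10% with 156 per arm. These figures assume a single unadjusted comparison, as in the protocol's own calculation; the planned mixed model may do better. The SD of 15.8 is the protocol's value and not a floor, since weakly correlated scales could give a smaller one.

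The documents do not support saying that the trial will declare equivalence from a non-significant test, or that it can say nothing useful on these outcomes. The point concerns stated secondary hypotheses, should be settled before analysis, and leaves the primary endpoint unaffected. Continuity of care stands in the same hypothesis list with the same gap; cost-effectiveness has its own framework.

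**What to change.** 1. For the patient-reported outcomes, drop the wording about not differing significantly, and state that p > 0.05 will not be read as equivalence.
2. For the APECC mean score, conclude equal effectiveness only if the confidence bound from the planned mixed model excludes a prespecified margin at one stated one-sided level. The protocol's 8.1 points is the natural candidate, but it was introduced as a difference to detect, so the sponsor must justify it clinically as a margin and not choose it to suit the sample size.
3. Restate the APECC power paragraph as power to exclude that margin. At 60 per arm and one-sided 5%, this is 87% at SD 15.8 and 64% at SD 21.9. State whether the analysis covers radiotherapy patients only or all patients.
4. For quality of life, anxiety and the remaining scales, either prespecify a clinically justified margin for a lead score, or report differences with 95% confidence intervals as estimates and make no claim of equal effectiveness.

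The cost is wording in the protocol or statistical analysis plan before analysis. The data and models stay the same and no patients are added. The downside is that some outcomes may end as inconclusive, and for the APECC score this becomes more likely as the SD rises towards 21.9.
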